## Abstract

**Background::**

Cervical spondylotic myelopathy (CSM) is the most serious type of cervical spondylosis, which is often treated surgically in patients with progressive neurological symptoms following ineffective conservative treatment. However, some patients have residual symptoms such as neck pain, stiffness, and C5 nerve palsy after surgery. The Qishe pill can effectively relieve the symptoms of neck pain and numbness, but there is no evidence showing the efficacy and safety of the Qishe pill in treating symptoms after spinal cord surgery.

**Methods/design::**

A multicenter, randomized controlled clinical trial will be conducted to evaluate the efficacy and safety of the Qishe Pill. A total of 330 patients with CSM who receive surgical treatment will be randomly divided into 2 groups, treated for 12 weeks and with a 1-year follow-up. The primary outcome will be Japanese Orthopaedic Association score from the baseline to 4 weeks, 12 weeks, 24 weeks, and 48 weeks after surgery. Secondary outcomes will include Visual Analogue Scale score, Neck Disability Index, and imaging indicators (including magnetic resonance imaging and X-ray). Additionally, adverse reactions will be observed and recorded as safety indicators.

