### Sample size calculation

2.4

On the basis of the comparison treatment, we calculated the sample size of the 2 groups (Qishe pill versus Methycobal), which will be randomly distributed in an equal manner. Since Japanese Orthopaedic Association (JOA) scores can include sensory and motor function of the limbs and bladder, we chose JOA scores to calculate the sample size with an estimated correlation coefficient of the measurements of ρ=0.8 and with an alpha = 0.05. The JOA score was 13.68 ± 1.83 at the 6-month follow-up after oral administration of Methycobal, and 15.65 ± 1.61 at the 6-month follow-up after oral administration of traditional Chinese medicine for promoting blood circulation and removing blood stasis, so the calculated sample size of each group is 132. Considering a 20% loss to follow-up, the total sample size needed to detect this difference at a 5% level of significance with a power of 90% is 330 patients.

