#### Primary outcomes

2.7.1

The primary outcomes include the items:

JOA scores assessed the patients’ cervical spine function based on the sensation and movement of the limbs, sensation of the chest and abdomen, and bladder function. In addition, the improvement rate of JOA will be compared.^[14]^ 

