### Statistical analysis

2.12

Statistical analysis includes statistical description and statistical inference. The statistical description of quantitative index includes mean, standard deviation, median, minimum, and maximum. The qualitative index is described by frequency table and composition ratio. Statistical inference includes interval estimation and hypothesis testing.

All statistical analysis will be conducted by Statistical Packages of Social Sciences software (version 22.0). By the bilateral test, *P* < .05 will be considered to be statistically significant. The mean ± standard deviation will be used for the description of continuous variables. Continuous variables following the normal distribution will be analyzed by Student *t*-test. The non-normally distributed data will be tested using the rank sum test. The non-grade data in the counting data will be tested with the 2 test or the non-parametric test. The grade data will be checked by Ridit.

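### The primary outcome is several comparisons, defined differently in three places, with no primary time point; if any one significant result may count, the four JOA visits carry a two-sided error of about 11% to 13% at correlation 0.8, not 5%

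*Protocol article*

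**What the plan says.** Four places in the protocol article bear on the primary comparison.

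- **Abstract, Methods/design:** "The primary outcome will be Japanese Orthopaedic Association score from the baseline to 4 weeks, 12 weeks, 24 weeks, and 48 weeks after surgery". That is four post-baseline visits, none singled out.
- **Section 2.7.1 (Primary outcomes):** opens with "The primary outcomes include the items", describes the JOA score, and continues: "In addition, the improvement rate of JOA will be compared". No visit is named for either measure, and the abstract does not mention the improvement rate.
- **Section 2.4 (Sample size calculation):** uses JOA means and SDs at one time only. The control value is "at the 6-month follow-up after oral administration of Methycobal", and the experimental value is at the same follow-up. Alpha is 0.05, power 90%, and a correlation of 0.8 between measurements is mentioned.
- **Section 2.12 (Statistical analysis):** "By the bilateral test", P "< .05 will be considered to be statistically significant". For normally distributed continuous variables it names Student's t-test, otherwise a rank sum test.

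Sections 2.1 and 2.10 put the end of treatment at week 12 and the last visit at week 48.

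**The concern.** The three descriptions of the primary outcome do not coincide: the score at four visits, the score plus an improvement rate at unstated visits, and one 6-month score. A reader of the final report could not tell from the article which result decides the trial.

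This matters in two ways. First, if success may be declared on whichever primary comparison reaches P < .05, the 5% error rate behind the sample size no longer applies to the trial's conclusion. Second, the visits answer different questions. Week 12 is the end of treatment and week 48 is 36 weeks later. A difference at one and none at the other is quite possible, and the article has no rule for which prevails.

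**Working it through.** **The plan's own figures.** The step from 132 per group to the total reproduces: 132 / 0.8 = 165, and 165 × 2 = 330. The 132 itself does not follow from the 6-month values as a two-sample comparison of means:

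- difference = 15.65 − 13.68 = 1.97
- SD = √((1.83² + 1.61²)/2) = 1.72
- n = 2 × (1.960 + 1.282)² × 1.72² / 1.97² = 16.1, so 17 per group

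That is a separate matter and does not affect the error rates below. What matters here is that section 2.4 uses one time point and one alpha.

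**Inputs for the error rate**

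- Four JOA comparisons at weeks 4, 12, 24 and 48 (abstract).
- Two-sided 0.05 for each, critical value 1.96 (section 2.12).
- Correlation 0.8. Section 2.4 gives this figure without saying which pairs of measurements it describes. Using it between post-baseline visits is an assumption, so 0.5 and 0.9 are shown as well.
- Decision rule: success if at least one comparison is significant. This too is an assumption.

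**Formula.** Under no effect the four test statistics are approximately multivariate normal, with the correlation of the visits. The family-wise error is P(at least one |Z| > 1.96). It was obtained by simulation (one million draws) with equal correlation between all visits and with correlation that decays with distance (autoregressive). As limits, four independent tests give 1 − 0.95⁴ = 18.5%, and four perfectly correlated tests give 5%.

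| Four JOA visits, correlation | Equal | Autoregressive |
|---|---|---|
| 0.9 | 9.4% | 10.4% |
| 0.8 | 11.4% to 11.5% | 12.6% to 12.7% |
| 0.5 | 15.6% | 16.6% |

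The 0.5 row is relevant if the abstract means change from baseline. With all five measurements equally correlated at 0.8, two change scores that share a baseline correlate at (0.8 − 0.8 − 0.8 + 1) / (2 − 2 × 0.8) = 0.2 / 0.4 = 0.5.

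**One direction only.** Counting only false results in favour of Qishe (Z > 1.96), four visits at 0.8 give 5.7% to 6.3%. The matching nominal value is 2.5%.

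**Adding the improvement rate.** Section 2.7.1 gives neither its visits nor its formula. Trials were simulated with 132 per group, correlation 0.8, assumed JOA means and an assumed rate of (post − pre)/(17 − pre):

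- the four JOA visits alone: 11.6%
- plus the rate at one visit: 13.2%
- plus the rate at all four visits: 18.4%

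A direct calculation for eight tests, with equal visit correlation 0.8 and an assumed score-to-rate correlation of 0.9 down to 0.5, gives 15.6% to 20.0%.

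**After a fix.** One named comparison gives 5% with no change in N. Splitting alpha over four visits (0.05 / 4 = 0.0125 each) gives at most 5%. With 132 per group the difference detectable with 90% power is √(2 × (1.960 + 1.282)² / 132) = 0.40 SD, or 0.40 × 1.72 ≈ 0.69 points. At that difference the split lowers power at a single visit from 90% to about 77%: the critical value rises to 2.498, and 3.242 − 2.498 = 0.744. At the assumed 1.97 points, power stays above 99.9%.

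**The case against.** **The any-one-wins rule is not in the article.** Correct. The error rates are conditional on it. But the article does not exclude it either, and naming several primary comparisons without a deciding one is what leaves it open.

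**The tests may not be separate.** Section 2.12 is a general paragraph that does not mention visits. The abstract uses the singular, and section 2.4 cites a correlation between measurements. All of this could fit one repeated-measures comparison. That reading is possible, but no such method is named, and the methods that are named compare two groups on one variable at a time.

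**A statistical analysis plan may settle it.** Multiplicity adjustment and testing order are commonly left to that plan, so their absence here is not the point. Which outcome and visit are primary is something this article does fix, and it fixes it in three ways that do not agree.

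**A stronger reading is tempting:** that the chance of a false efficacy claim is 11% to 20% instead of 5%. The document does not support that. Those figures count false differences in either direction, and a false claim for Qishe is about half as likely. They also presuppose the any-one-wins rule. The upper part needs the improvement rate to be tested at all four visits, which section 2.7.1 does not say.

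**Conclusion.** The point stands as an inconsistent and plural definition of the primary outcome. No primary time point is fixed, the abstract and section 2.7.1 differ on the improvement rate, and the sample size matches neither.

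The consequence for error control is conditional. With the four JOA visits, any one of which may count, the two-sided error is roughly double the nominal 5% at a correlation of 0.8 to 0.9, and about three times it at 0.5. In the direction of a Qishe benefit at 0.8, it is a little over double the nominal 2.5%. Values near 20% at 0.8 rest on a further assumption about the improvement rate and should not be quoted as the plan's error rate. The exact size depends on the correlation and the number of tests, neither of which the article pins down. Within the range examined it does not return to 5%.

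**What to change.** Before any results are seen, name one primary comparison and state it identically in the abstract, section 2.7.1 and section 2.4. The between-group difference in JOA score at week 24 is the natural choice, because it is the visit nearest the 6-month basis of the sample size. The other visits and the improvement rate then become secondary.

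Week 24 is not the only acceptable answer. If the sponsor wants all visits to stay primary, one joint repeated-measures test or a split of alpha across visits would also control the error, and section 2.12 should then name it. The role and visits of the improvement rate should be stated either way.

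Naming one comparison costs wording only: no new data and no change in N. The sponsor gives up the option of claiming success at any single visit. A split alpha carries the loss of power shown in the working if the true difference is near 0.69 points.

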**Discussion::**

Although the Qishe pill can effectively improve the discomfort of the neck and upper limbs in clinical applications, there is a lack of clinical research on postoperative patients. This study will investigate the efficacy and safety of the Qishe pill in treating postoperative symptoms of CSM.

**Trial registration::**

Clinical Trials.gov ID: ChiCTR1900028173. Registered on 17 December 2019.

## Introduction

1

Cervical spondylotic myelopathy (CSM) often presents with symptoms that are related to dysfunction of the spinal cord, caused by the degeneration of the cervical vertebrae (such as intervertebral disc, ligaments, osteophytes) and related secondary changes (excessive activity of the cervical vertebrae and cervical instability).^[1,2]^ By age 50, magnetic resonance imaging (MRI) showed that as many as 31.6% of the population had spinal cord compression, rising to 66.8% after age 80.^[3]^ Progressive CSM can cause a range of symptoms such as limb numbness, walking instability, and bundle sensation, and 20% to 60% of spinal or neurological symptoms can worsen without surgery.^[4,5]^ Therefore, an increasing number of patients are receiving surgical treatment because it can relieve nerve compression, stop the progression of nerve damage, and improve function and quality of life. Although surgery is usually safe and effective, complications occur in 11% to 38% of patients. Fehlings et al^[6]^ found that overall perioperative and delayed complication rates were 15.6% and 4.4%, respectively. Most complications are temporary and non-neurological. No invasive intervention or prolonged hospital stay is required. However, some patients have intractable neck pain, limb numbness, and even muscle weakness after surgery.^[7,8]^

The Qishe pill is a Chinese medicine consisting of processed Radix Astragali, Muscone, Szechuan Lovage Rhizome, Radix Stephaniae Tetrandrae, Ovientvine, and Calculus Bovis Artifactus, and has the function of regulating qi and promoting blood circulation, regulating collaterals, and relieving pain.^[9,10]^ Related studies showed that it can effectively relieve cervical pain and numbness, and improve quality of life in patients with CSM.^[11,12]^ It has been found in clinical practice that the Qishe pill can improve postoperative symptoms of CSM to some extent, but there is still a lack of evidence to prove this. Therefore, we designed a multicenter, randomized, clinically controlled trial to demonstrate its efficacy and safety.

## Materials and methods

2

### Study design

2.1

This is a multicenter, randomized clinical trial with 2 parallel arms (Fig. 1). We will recruit 330 patients from 2 medical institutions in Shanghai, China: Longhua Hospital Affiliated with Shanghai University of Traditional Chinese Medicine, and Long March Hospital Affiliated with Second Military Medical University. All patients will be randomly assigned to either an experimental group or a control group. Patients in the experimental group will be required to take the 3.75-g Qishe pill twice daily after breakfast and dinner, and patients in the control group will take 1 Methycobal tablet 3 times daily. All drugs will be administered orally for 12 weeks.

**Figure 1 F1:**
[figure not shown]
Project overview.

### Ethical issues

2.2

The trial will be conducted in accordance with the Declaration of Helsinki and Ethical Guidelines for Clinical Research, and the trial protocol has been approved by the Research Ethical Committee of Longhua Hospital Affiliated with Shanghai University of Traditional Chinese Medicine, Shanghai, China, (approval number: 2019LCSY081).

All patients will be informed of the protocol, the purpose of the trial, and the rights, obligations, and risks involved with participation in the trial. Only patients who fully understand and sign the informed consent form will participate in the trial. In addition, the personal information about potential and enrolled subjects will not be shared or maintained if unnecessary.

### Study participants

2.3

We will recruit patients using posters and from outpatient and inpatient departments from 2 hospitals (LongHua Hospital Affiliated with Shanghai University of Traditional Chinese Medicine and Long March Hospital Affiliated with Second Military Medical University). The planned recruitment period is 12 months.

### Sample size calculation

2.4

On the basis of the comparison treatment, we calculated the sample size of the 2 groups (Qishe pill versus Methycobal), which will be randomly distributed in an equal manner. Since Japanese Orthopaedic Association (JOA) scores can include sensory and motor function of the limbs and bladder, we chose JOA scores to calculate the sample size with an estimated correlation coefficient of the measurements of ρ=0.8 and with an alpha = 0.05. The JOA score was 13.68 ± 1.83 at the 6-month follow-up after oral administration of Methycobal, and 15.65 ± 1.61 at the 6-month follow-up after oral administration of traditional Chinese medicine for promoting blood circulation and removing blood stasis, so the calculated sample size of each group is 132. Considering a 20% loss to follow-up, the total sample size needed to detect this difference at a 5% level of significance with a power of 90% is 330 patients.

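### The printed JOA inputs give 17 to 18 patients per group, not 132, so the claim that 330 are needed for 90% power to detect 1.97 points is wrong

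*Protocol article*

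**What the plan says.** Section 2.4 (Sample size calculation) bases the trial size on the JOA score. The control input is given as "The JOA score was 13.68 ± 1.83 at the 6-month follow-up after oral administration of Methycobal" and the experimental input as "15.65 ± 1.61 at the 6-month follow-up after oral administration of traditional Chinese medicine for promoting blood circulation and removing blood stasis". The calculation is said to have been done "with an estimated correlation coefficient of the measurements of ρ=0.8 and with an alpha = 0.05", with equal allocation. The text then goes straight to the result: "so the calculated sample size of each group is 132". After allowing for 20% loss to follow-up it concludes that "the total sample size needed to detect this difference at a 5% level of significance with a power of 90% is 330 patients".

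Section 2.12 (Statistical analysis) makes the tests two-sided and names Student's t-test for normally distributed continuous variables. Section 2.10 lists five visits: baseline and weeks 4, 12, 24 and 48. No smaller target difference, no margin, and no formula showing the role of ρ is given.

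**The concern.** A difference of almost 2 points against SDs of 1.6 to 1.8 is a standardised effect above 1. An effect that large needs a few dozen patients in total, not several hundred. The article nevertheless presents 132 per group as following from these inputs.

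The danger is not too few patients. The target difference and the power will be cited when the result is read, and here they do not belong together. A reader told that the trial was sized for a 1.97-point benefit could take a significant result as confirming a benefit of that order, when a much smaller observed difference would also be significant. In addition, if 1.97 points really is the target, the calculation given does not justify enrolling 330 surgical patients.

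**Working it through.** **Inputs.** Means 13.68 and 15.65, SDs 1.83 and 1.61, α = 0.05, power 90%, 1:1 allocation, ρ = 0.8 and 20% loss, all from section 2.4. Two-sided testing and the t-test are from section 2.12.

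**The plan's own figure.** The loss step reproduces: 132/0.80 = 165 per group, 330 in total. The fault therefore lies in the step to 132.

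**Sample size for the stated difference**
- Difference: 15.65 − 13.68 = 1.97.
- Pooled variance: (1.83² + 1.61²)/2 = 2.9705, so SD = 1.7235.
- Standardised effect: 1.97/1.7235 = 1.143.
- Normal approximation: n = 2 × 2.9705 × (1.960 + 1.2816)² / 1.97² = 16.1, so **17 per group**.
- Noncentral t: power is 0.898 at 17 and 0.915 at 18, so **18 per group**.
- After 20% loss: 18/0.8 = 22.5, so 23 per group and 46 in total.

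**Attempts to reach 132**

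| Variant | n per group |
|---|---|
| SD 1.61 instead of pooled | 15 (normal), 16 (t) |
| SD 1.83 instead of pooled | 19 (normal), 20 (t) |
| Power 95% | 20 |
| Rank test, worst-case efficiency 0.864: 18/0.864 | 21 |
| ρ as baseline correlation, ANCOVA: 16.1 × (1 − 0.64) | 6 |
| ρ for change scores: 16.1 × 2(1 − 0.8) | 7 |
| ρ for the mean of 4 visits: 16.1 × (1 + 3 × 0.8)/4 | 14 |
| ρ misused as inflation, 4 visits: 16.1 × 3.4 | 55 |
| ρ misused as inflation, 5 visits: 16.1 × 4.2 | 68 |
| The two SDs added and used as the SD | 65 |

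One multiplier does give 132: 16.085 × (1 + 9 × 0.8) = 16.085 × 8.2 = 131.9. That is a design effect for clusters of ten. This trial randomises individuals and has five visits.

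**What 132 per group delivers**
- Standard error of the difference: 1.7235 × √(2/132) = 0.212.
- Power for 1.97 points: above 99.99%.
- Difference detectable with 90% power: (1.960 + 1.2816) × 0.212 = 0.688, or 0.690 with the t distribution. With the normal approximation it is 0.64 at SD 1.61 and 0.73 at SD 1.83.
- Smallest observed difference reaching P < .05: 1.97 (the t critical value on 262 df) × 0.212 ≈ 0.42 points.
- SD at which 132 per group would give 90% power for 1.97 points: 1.97 / (3.2416 × √(2/132)) ≈ 4.94, nearly three times the printed SDs.

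**The case against.** The best case against grants the arithmetic and disputes its weight.

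- **The error is harmless to power.** This is true. No conclusion is endangered by too few patients, and enrolment need not change. The stated power and target difference are still false as printed.
- **The figure of 0.69 is back-solved.** It is, and no section names it as a target. The authors may have used an unstated smaller difference, another method, or a misapplied inflation by ρ, which the match at 8.2 makes possible. So 0.69 should be read as what 132 per group can detect, not as what the sponsor intended. None of these origins would make the printed sentence correct.
- **A journal article condenses.** The role of ρ could be left to a fuller protocol. But the article does more than omit a step: it prints the inputs, derives 132 from them and asserts power for that difference.
- **Misreading is speculative.** Interval estimation is planned and would show a small effect as small, and every well-powered trial can reach significance below its target. That softens the consequence without removing it.
- **The total is not settled.** Section 2.6 speaks of 288 patients. This is a separate inconsistency, since 330 stands in the abstract and in sections 2.1 and 2.4. At 288 with 20% loss (288 × 0.8/2 ≈ 115 per group) the detectable difference would be about 0.74 points, so the total has to be reconciled before the figure is final.
- **Naming week 24 might seem to choose a primary time point.** It only matches the 6-month planning data, and the rewording can say so.

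**Conclusion.** The concern holds. From the printed means and SDs, a two-sided 5% two-group comparison with 90% power needs 17 to 18 patients per group. The stated 132 is 7.3 times 18, 7.8 times 17, or 8.2 times the unrounded 16.1. Power for 1.97 points at 132 per group is effectively 100%, and 90% power corresponds to about 0.69 points, 35% of the stated difference (0.69/1.97).

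This assumes that the difference meant is the 1.97 points between the two quoted means, the only one given, and that the comparison is the two-sided t-test in section 2.12. The choice of SD, a rank test, or any standard use of ρ does not change the conclusion. The trial is not underpowered; what is wrong is the justification of its size and the effect it claims to be sized for.

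**What to change.** Keep 330 and correct the paragraph in section 2.4, for example: *With 132 evaluable patients per group, a two-sided 5% two-sample comparison has 90% power to detect a difference of 0.69 JOA points at week 24 (SD 1.72; week 24 corresponds to the 6-month planning data).*

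Delete ρ, or state which correlation it is and how it enters. If it is a baseline-to-follow-up correlation and the analysis becomes baseline-adjusted ANCOVA, the detectable difference is 0.69 × √(1 − 0.64) = 0.41 points. If 132 came from a different target difference, SD or formula, print that derivation instead.

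It would also help to state the smallest JOA difference the sponsor regards as worthwhile, so that a significant but small difference is not read as efficacy.

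The cost is the rewording of one paragraph. Enrolment does not change; the stated target difference does.
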